## Outcomes

3

### Primary outcomes

3.1

WSBM is assessed by recording the number of naturally occurring bowel movements within a week (25). This indicator was selected as the primary outcome due to the high incidence and recurrence of paralytic ileus in patients with severe stroke. Scores range from 0 upward, with higher scores indicating better recovery of intestinal function (26).

### Secondary outcomes

3.2

Assessment of Bowel Movement Regularity involves daily monitoring of spontaneous bowel movements over a week. A score of 1 is assigned for each day with a spontaneous bowel movement occurring without the use of emergency medication and without diarrhea, while a score of 0 is given if no bowel movement occurs, if emergency medication is used, or if diarrhea is present. The total score ranges from 0 to 7, with higher scores indicating better bowel movement regularity and overall intestinal function.

Rescue medication will be carefully recorded throughout both the treatment and follow-up periods, with detailed documentation of the frequency, dosage, and timing of administration. Increased use of rescue medication will be considered a potential indicator of the severity and recurrence rate of gastrointestinal dysmotility.

Bowel sounds are assessed via auscultation with the patient in a supine position. Each abdominal quadrant (right upper, right lower, left lower, and left upper) is auscultated for 1 min, and the average frequency is calculated. Within a physiologic range, higher average bowel sound frequencies indicate better intestinal motility and recovery (4).

Abdominal circumference is measured to assess distension and gastrointestinal function recovery. With the patient supine and relaxed, a measuring tape is placed horizontally at the umbilicus level, snug but not compressing the skin. The measurement, recorded in centimeters (cm), is taken at the end of gentle exhalation, repeated twice, and averaged. Higher values indicate severe distension and impaired function, whereas lower values suggest improvement. A decrease over time is considered favorable (27).

GCS is used to evaluate neurological status, monitor changes in consciousness, and predict prognosis. It assesses consciousness through three components: eye response, verbal response, and motor response (28). The total score ranges from 3 to 15, with higher scores indicating better consciousness and neurological function.

NIHSS is used to evaluate the severity of neurological deficits in stroke patients. It consists of 15 items assessing consciousness level, language ability, visual fields, motor function, sensory function, ataxia, and coordination (29). Scores range from 0 to 42, with higher scores indicating more severe neurological impairment and greater stroke severity.

mRS is used to evaluate long-term functional outcomes and quality of life after stroke (29). It assesses disability and dependence, ranging from 0 (no symptoms) to 6 (death), with higher scores indicating greater functional impairment.

Length of hospitalization, measured from admission to discharge, reflects overall recovery. Shorter stays indicate better outcomes, while prolonged stays suggest delayed recovery and greater dysfunction. Further details of standardized outcome assessment procedures are provided in Supplementary material.

Study outcomes are summarized in Table 1.

**Table 1 tab1:** Overview of study outcomes.

Outcome	Data range	Interpretation
Primary outcomes		
Weekly spontaneous bowel movements	≥0 (times/week).	Higher values indicate better intestinal function.
Secondary outcomes		
Bowel movement regularity	0–7 (score/week).	Higher scores indicate better regularity.
Rescue medication use	-	More use indicates worse symptoms.
Bowel sounds	≥0 (times/min).	Higher frequency indicates better motility.
Abdominal circumference	-	Lower values suggest improvement over time.
Glasgow coma scale	3–15 score.	Higher scores indicate better consciousness.
National institutes of health stroke scale	0 - 42score.	Higher scores indicate more severe impairment.
Modified rankin scale	0–6 score.	Higher scores indicate greater disability.
Length of hospitalization	3–45.	Shorter stay indicates faster recovery.

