## Introduction

1

Stroke ranks as the third leading cause of death and the fourth leading cause of disability-adjusted life-years (DALYs) worldwide (1). Among its complications, gastrointestinal dysfunction, particularly paralytic ileus, is a major concern in severe stroke cases (2, 3). Paralytic ileus, characterized by absent stool passage for three or more consecutive days without mechanical obstruction (4), affects over 40% of severe stroke patients (5, 6) and is commonly mistaken for constipation. In this vulnerable population, factors such as immobility, autonomic dysfunction, and medication side effects predispose to paralytic ileus (7). It contributes to abdominal distension, heightened risks of infection and malnutrition, and impairs neurorecovery by restricting rehabilitation and aggravating inflammation, placing considerable strain on patients and healthcare systems (8, 9).

Despite its clinical importance, paralytic ileus treatment remains conservative—nasogastric decompression, supportive care, and prokinetics (4, 5). Yet decompression poorly restores motility (10). Options like coffee or gum chewing aid recovery (11, 12) but face limitations in stroke patients: coffee may cause agitation; gum chewing is impractical in unconscious cases. Prokinetics, though common, show variable efficacy and risk of dependency or resistance (13–15). These limitations highlight the pressing need for safer and more efficacious therapeutic alternatives.

Electroacupuncture (EA), a type of acupoint stimulation therapy, has demonstrated potential in regulating autonomic function, enhancing gastrointestinal motility, and optimizing neurological outcomes (16, 17). Clinically, EA is proven to enhance postoperative bowel recovery, particularly in abdominal surgery cases, through improved gut motility (18, 19). However, current evidence for acupoint therapy in stroke ileus is weak, hampered by methodological issues such as inappropriate sham acupuncture controls or insufficient blinding (20, 21). Furthermore, severe stroke patients exhibit the highest incidence of paralytic ileus, yet EA’s therapeutic efficacy in this specific population remains largely unexplored.

Given these considerations, we have designed a randomized controlled trial (RCT) to assess the safety and efficacy of EA in alleviating paralytic ileus in patients with severe stroke.

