#### Inclusion criteria

2.2.1

Participants must meet the following criteria to be included in the study:Diagnosis of severe stroke as defined by clinical assessment, with a Glasgow Coma Scale (GCS) score ≤ 12.Clinically confirmed diagnosis of paralytic ileus, with the requirement of enteral nutrition for more than 48 h.Age between 18 and 65 years, regardless of gender.Stable vital signs for at least 24 h, with an Acute Physiology and Chronic Health Evaluation II score < 31.For patients unable to provide informed consent, permission will be obtained from a direct family member before inclusion in the study.

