#### Follow-up

2.4.5

Patients will have video or in-person follow-ups at Weeks 4 (2 weeks after treatment) and 6 (4 weeks after treatment).

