### Data management

2.5

Study data will be recorded on case report forms (CRFs) by assessors, with participants identified by randomization numbers. Two independent staff will perform double data entry. The data management system will validate entries for range and logic errors. All data will be encrypted, with access restricted to authorized personnel. Paper CRFs will be securely stored at the South China Research Center for Acupuncture and Moxibustion for no less than three years after the completion of the study.

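### Length of hospitalization is counted from admission, so it includes pre-randomisation days that treatment cannot affect and loses precision; the 3–45 range in Table 1 also needs a unit and a check against that clock

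*Protocol article*

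**What the plan says.** **Definition.** Section 3.2 of the protocol article states: "Length of hospitalization, measured from admission to discharge, reflects overall recovery". Table 1 gives the data range as 3–45 without a unit and adds the reading "Shorter stay indicates faster recovery".

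**Entry.** Section 2.2.1 requires "Clinically confirmed diagnosis of paralytic ileus, with the requirement of enteral nutrition for more than 48 h" and "Stable vital signs for at least 24 h". The Introduction describes paralytic ileus as "characterized by absent stool passage for three or more consecutive days without mechanical obstruction".

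**Timing.** Table 2 marks length of hospitalization only in the Week 6 column. Section 2.4.5 places Week 6 four weeks after the end of treatment, and treatment ends at Week 2.

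**Analysis.** Section 2.8 compares stay between groups with an independent t-test or a Mann–Whitney U test, depending on distribution, and names no covariate. The same section makes weekly spontaneous bowel movements the only confirmatory endpoint and treats all secondary outcomes as exploratory.

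**Data checks.** Section 2.5 says: "The data management system will validate entries for range and logic errors". It does not say which limits are used.

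**The concern.** A randomised comparison of stay is informative about treatment only through the days after randomisation. Starting the clock at admission adds an interval that was complete before allocation. The entry criteria mean that this interval is not zero for typical patients: ileus has to be recognised and confirmed, and vital signs have to have been stable for 24 h.

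Those days add variance to the outcome without adding any treatment signal. Because the planned tests are unadjusted, a chance difference between arms in time from admission to randomisation passes one-for-one into the difference in mean stay. With about 50 patients per arm, that difference need not be small compared with an effect of a few days.

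The Table 1 range raises a smaller question of consistency. If 3–45 means days and is meant as a limit, it has to hold for a stay that starts at admission and is read at Week 6.

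**Working it through.** **Inputs from the document:** clock from admission to discharge (section 3.2); range 3–45 (Table 1); Week 6 as the only recorded time point (Table 2); treatment ending at Week 2 and Week 6 falling 4 weeks later (section 2.4.5); 100 participants allocated 1:1, so 50 per arm (sections 2.3 and 2.7).

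**Assumed, because the document gives no figure:** SD of post-randomisation stay 10 days; SD of days from admission to randomisation 3, 5 or 10 days; the two intervals independent; randomisation and start of treatment on the same day; range in days.

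**1. Precision.** Total stay = pre-randomisation days + post-randomisation days.
- Variance ratio = 1 + SDpre² / 10².
- Information kept = 1 / variance ratio.
- SE of the arm difference = √(10² + SDpre²) × √(2/50).
- SE of the chance difference from pre-randomisation days alone = SDpre × √(2/50) = SDpre × 0.2.

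| SDpre (days) | Variance ratio | Information kept | SE of arm difference (days) | SE from pre-randomisation days alone (days) |
|---|---|---|---|---|
| 0 | 1.00 | 1.00 | 2.00 | 0 |
| 3 | 1.09 | 0.92 | 2.09 | 0.6 |
| 5 | 1.25 | 0.80 | 2.24 | 1.0 |
| 10 | 2.00 | 0.50 | 2.83 | 2.0 |

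**2. Power, as an illustration only.** With an assumed true difference of 5 days, 50 per arm and two-sided 0.05, power is 0.71 for SDpre 0, 0.67 for 3, 0.61 for 5 and 0.42 for 10.

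**3. Dependence on independence.** If the two intervals have correlation ρ, the variance ratio gains the term 2ρ × SDpre / 10. A positive ρ makes the inflation larger. It disappears only at ρ = −SDpre / 20, that is −0.15, −0.25 or −0.50 for SDpre of 3, 5 or 10.

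**4. The range.** Week 6 = 14 + 28 = day 42 from the start of treatment. A patient enrolled k days after admission and still in hospital then has a stay of at least k + 42 days:
- k = 3: at least 45
- k = 4: at least 46
- k = 7: at least 49
- k = 14: at least 56

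Since 45 − 42 = 3, the upper figure leaves room for about three days before enrolment. The threshold moves by one day with the counting convention: if admission is hospital day 1 and nights are counted, enrolment on hospital day 4 gives 3 + 42 = 45. The figure k + 42 is a minimum for patients still in hospital; a patient enrolled later but discharged before Week 6 can have any shorter total. Counted from randomisation, a patient still in hospital at Week 6 stands at 42 days whatever k is.

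**The case against.** The case on the other side is substantial, and much of it stands.

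- **No bias.** A reader might infer that the definition distorts the comparison or manufactures an effect. It does not. Pre-randomisation days are balanced in expectation, and chance imbalance is already reflected in the standard error, so the test keeps its nominal error rate.
- **Low stakes.** The outcome is exploratory. The Discussion mentions shorter hospitalization only as a possible consequence of positive results, so it should not be read as a claim that depends on this comparison.
- **Assumed size.** Every SD above is an assumption. At an SDpre of 3 days the SE rises only from 2.00 to 2.09. Halving the information requires pre-randomisation days to vary as much as the stay that follows.
- **Unknown pre-randomisation time.** The entry conditions can overlap, days without stool may begin before admission, and the enteral nutrition wording may mean a need rather than elapsed time. A minimum number of hospital days before entry therefore cannot be derived. The article states no limit on time from admission to enrolment, but that may stand in the full protocol and is not counted against it here.
- **The range.** A reader might infer that 3–45 is a cap that would reject correct long stays. The document does not support this: the range has no unit, may be an expected range, is not linked to the checks in section 2.5, and conflicts only for patients still in hospital at Week 6. How common such patients will be is not stated.
- **Total stay is legitimate.** It is a recognised measure of hospital burden and is clearly defined.

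None of this removes the main point. The start of the clock is stated explicitly, so it is not a detail left to another document, and the stated analysis does nothing to take the earlier days out.

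**Conclusion.** The point holds as a matter of efficiency on an exploratory endpoint. Length of hospitalization as defined includes time that treatment cannot affect, and the unadjusted comparison carries that time into the result. Under an assumed post-randomisation SD of 10 days and independence, the variance rises by 9%, 25% or 100% for a pre-randomisation SD of 3, 5 or 10 days, and the pre-randomisation days alone contribute a chance arm difference with an SE of 0.6, 1.0 or 2.0 days. The true position within that range, or outside it, cannot be settled from the document. The validity of the test is not in question. The change is worth making because it costs almost nothing.

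The 3–45 range is secondary. It sits poorly with an admission-based clock read at day 42 if it is a limit in days, but neither condition is stated, so the appropriate request is for clarification and consistency.

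**What to change.** 1. Define the outcome in section 3.2 as days from randomisation to discharge.
2. Record days from admission to randomisation as a baseline variable and report it by arm.
3. Keep total stay from admission to discharge as a descriptive table.
4. In Table 1, state the unit and say whether the range is a limit or an expectation. Make it agree with the chosen start point and the Week 6 horizon, and use the same figures in any data check built on it.

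**Cost.** One definition and one table entry. The admission date is already needed for the present definition, and the randomisation date is held by the central system. The change can be made without unblinding. The small downside is less direct comparability with studies that report total stay, which the descriptive table largely covers.

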The primary outcome, WSBM, is a discrete quantitative variable assessed at multiple time points. Depending on the data distribution, either a linear mixed-effects model or a generalized linear mixed model will be used. Secondary outcomes with continuous repeated measures, such as bowel sound frequency, GCS, and the National Institutes of Health Stroke Scale (NIHSS), will be analyzed using linear mixed-effects models if the data are approximately normally distributed. Otherwise, generalized linear mixed models with appropriate distributions will be applied. Rescue medication use, as a count variable assessed over time, will be analyzed using generalized linear mixed models. The Modified Rankin Scale (mRS), being an ordinal variable assessed repeatedly, will be analyzed using ordinal logistic regression models for repeated measures. Length of hospital stay, a continuous variable, will be compared between groups using either the independent samples t-test or the Mann–Whitney U test, depending on distribution. Adverse events, as categorical variables, will be analyzed using the chi-square test or Fisher’s exact test, depending on the expected cell counts. The primary outcome will be analyzed as the sole confirmatory endpoint, while all secondary outcomes will be treated as exploratory. For repeated measures, *post hoc* correction will be applied, but no formal multiplicity adjustment will be conducted across multiple secondary endpoints. Additional statistical analyses are provided in the Supplementary material.

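### Length of hospitalization is read as better when shorter and compared by t-test or Mann–Whitney U, with no provision for patients who die in hospital or are not discharged by Week 6

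*Protocol article*

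**What the plan says.** Section 3.2 (Secondary outcomes) of the protocol article defines the measure and its direction: "Length of hospitalization, measured from admission to discharge, reflects overall recovery", and then "Shorter stays indicate better outcomes, while prolonged stays suggest delayed recovery and greater dysfunction". Table 1 repeats the direction ("Shorter stay indicates faster recovery") and gives a data range of 3–45 with no unit. Neither place makes the favourable reading depend on being discharged alive.

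Section 2.8 (Statistical analysis) treats the stay as a continuous variable that "will be compared between groups using either the independent samples t-test or the Mann–Whitney U test, depending on distribution". The same section puts every randomised patient in the intention-to-treat set, names weekly spontaneous bowel movements as the only confirmatory outcome, and calls all secondary outcomes exploratory.

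Table 2 marks length of hospitalization only at Week 6, which section 2.4.5 (Follow-up) places four weeks after treatment ends. Section 2.2.1 admits patients by "Diagnosis of severe stroke as defined by clinical assessment, with a Glasgow Coma Scale (GCS) score ≤ 12". Section 3.2 defines the modified Rankin Scale (mRS) so that its top score, 6, is death.

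**The concern.** A stay can end in two opposite ways: discharge alive or death. A rule that calls every short stay a good result is sound only if all stays end in discharge. This trial does not expect that, because its mRS reserves a category for death and its patients are severely ill. The same early death would be the worst possible mRS score and could be among the best lengths of stay.

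The two named tests need one complete number per patient. They have no means of separating a stay ended by death from one ended by recovery, and none of marking a stay as unfinished at Week 6. Someone will have to choose a value for these patients, and the article does not say which.

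The consequence is one of direction. If electroacupuncture reduced deaths, the surviving patients would lengthen its mean stay; if it increased deaths, the stay would look shorter. The Discussion (section 4) names shorter hospitalization among the possible benefits that could inform guidelines, so the result may be used.

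**Working it through.** **Plan's own figure.** The article states no figure for length of stay. Its sample size concerns the primary outcome and serves here only to set the arm size. The difference is 7.11 − 5.71 = 1.40 and the SD is √((2.20² + 1.50²)/2) = 1.883. At two-sided 0.05 and 90% power, the normal approximation gives 39 per group, and the unequal-variance t-test has power 0.906 at 40. So 40 is reproduced, and 40/(1 − 0.20) = 50 per arm gives the stated 100.

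**Two readings of the written rule for an in-hospital death.**

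1. *The day of death closes the stay.* An early death gives a low value, read as favourable.
2. *Death is not discharge.* The patient has no value and leaves the comparison, although the analysis set is everyone randomised. With 50 per arm and deaths of 10% and 20%, that is 0.10 × 50 = 5 and 0.20 × 50 = 10 patients, leaving 45 against 40, selected by an event after randomisation.

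**Size under reading 1, means.** The article gives no mortality, timing of death or expected stay, so all inputs are assumptions: survivors stay 28 days on average in both arms, and deaths occur on day 12.

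Mean stay = 28(1 − p) + 12p = 28 − 16p, where p is in-hospital mortality.

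| Mortality, EA v sham | Mean stay, EA | Mean stay, sham | EA minus sham |
|---|---|---|---|
| 10% v 10% | 26.4 | 26.4 | 0 |
| 10% v 20% | 26.4 | 24.8 | +1.6 days |
| 10% v 25% | 26.4 | 24.0 | +2.4 days |

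The shift is 16 × the mortality difference, or 0.16 day per percentage point, always against the arm with fewer deaths. A simulation with values bounded at 3–45 gave 1.55 and 2.41 days for the last two rows.

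**Size under reading 1, rank test.** A second illustration looks at the opposite direction, with more deaths on EA. All length-of-stay inputs are again assumptions: 50 per arm; the same log-normal stay in both arms (median 25 days, log-SD 0.5); deaths spread evenly over 14 days from enrolment; enrolment 3 days after admission; values capped at day 45; Mann–Whitney U; 4,000 runs. When ranked worst, deaths were coded one day beyond the cap, so mean differences in that coding are not days of stay.

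| Assigned death, sham v EA | Coding of death | Mean difference, EA − sham | Significant for EA | Significant for sham |
|---|---|---|---|---|
| 10% v 10% | day of death | −0.04 | 2.5% | 2.7% |
| 10% v 10% | ranked worst | −0.01 | 2.5% | 2.0% |
| 10% v 20% | day of death | −1.71 | 11.9% | 0.3% |
| 10% v 20% | ranked worst | +1.71 | 0.3% | 11.6% |
| 10% v 30% | day of death | −3.28 | 31.5% | 0% |
| 10% v 30% | ranked worst | +3.50 | 0% | 35.6% |

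With equal mortality the two-sided error rate stays near 5% under both codings. With unequal mortality, the coding of death decides which arm looks better.

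**Patients still in hospital.** In these runs, about 8–11% of patients were still in hospital at the cap, which again reflects the assumed stay. Week 6 is day 42 from the start of the study period, whereas the stay counts from admission. A patient admitted more than 45 − 42 = 3 days before that start and still in hospital at Week 6 already lies beyond the upper end of Table 1's range. The article does not say what value such a patient receives.

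**The case against.** The strongest reply is that this is silence, not error. Death is not named as an end of the stay, so the article does not literally score it as a success. Sections 2.8 and 3.2 refer to supplementary analyses and assessment procedures, and the Discussion promises to record intercurrent events and run sensitivity analyses; none of these is shown. Handling of deaths in a secondary outcome often sits in such documents. This limits severity, because a rule may exist there. It does not rescue what the article itself fixes: an unconditional reading of short stays, stated in both text and Table 1, and two tests that cannot take account of death or an unfinished stay.

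A reader might infer that patients still in hospital at Week 6 are treated as discharged. The documents do not support that. Table 2 shows when the outcome is recorded, not that stays are cut off there, and the 3–45 in Table 1 is a data range with no mention of a cap. Even if a cap were applied, such patients would already hold the longest and therefore worst ranks in a Mann–Whitney test, so this gap matters less than the one for deaths.

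A reader might also infer bias from starting the clock at admission. Days before randomisation are balanced in expectation; they add noise, not bias.

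Three further points stand. The outcome is exploratory. Deaths will be visible through the mRS at every visit. The sizes above rest on assumed mortality, and the protocol does not hypothesise a mortality effect; eligibility also requires stable vital signs and excludes severe heart, liver or kidney dysfunction.

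**Conclusion.** The point holds in this form: the article fixes the clock, the direction of benefit and the tests for length of hospitalization, and makes no provision for patients who die in hospital or are not discharged by Week 6. Followed as written, an early death becomes either a favourable value or a missing one, and both are unsound for a comparison of everyone randomised in a severe-stroke population.

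The illustrated shift is 1.6 days for a 10-point and 2.4 days for a 15-point mortality difference. In the rank-test illustration, the arm with more deaths is significantly favoured in about 12% of runs at a 10-point difference and 32% at a 20-point difference. These figures rest wholly on assumed mortality, timing of death and length of stay, and they apply where the day of death closes the stay. If mortality and the timing of deaths are alike in both arms, there is no distortion. It does not follow that the trial's length-of-stay result will be wrong, only that its direction is not protected. Because the outcome is exploratory, severity is minor to moderate.

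**What to change.** Define the outcome as time from randomisation to discharge alive, with in-hospital death as a competing event and patients still in hospital censored at last follow-up. Compare cumulative incidence of discharge alive between arms by Gray's test and report a subdistribution hazard ratio.

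A simpler alternative is to keep the Mann–Whitney test, drop the t-test, and rank in-hospital deaths worst and patients still in hospital at Week 6 next.

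Under either option:
- limit the favourable reading of a short stay, in section 3.2 and Table 1, to patients discharged alive;
- state what the 3–45 range means, its unit, and how a stay beyond it is recorded;
- report in-hospital mortality by arm beside the result.

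The cost is a change of wording, provided that discharge and death dates are recorded, which the article does not state explicitly. The drawback is a summary less familiar to clinicians than mean days; median stay among patients discharged alive can be shown descriptively, without a test.
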